## Abstract

**Background:**

Anastomotic leakage is a major complication in colorectal surgery and with an incidence of 11% the most common cause of morbidity and mortality. In order to reduce the incidence of anastomotic leakage the C-seal is developed. This intraluminal biodegradable drain is stapled to the anastomosis with a circular stapler and prevents extravasation of intracolonic content in case of an anastomotic dehiscence.

The aim of this study is to evaluate the efficacy of the C-seal in reducing anastomotic leakage in stapled colorectal anastomoses, as assessed by anastomotic leakage leading to invasive treatment within 30 days postoperative.

**Methods:**

The C-seal trial is a prospective multi-center randomized controlled trial with primary endpoint, anastomotic leakage leading to re-intervention within 30 days after operation. In this trial 616 patients will be randomized to the C-seal or control group (1:1), stratified by center, anastomotic height (proximal or distal of peritoneal reflection) and the intention to create a temporary deviating ostomy. Interim analyses are planned after 50% and 75% of patient inclusion. Eligible patients are at least 18 years of age, have any colorectal disease requiring a colorectal anastomosis to be made with a circular stapler in an elective setting, with an ASA-classification < 4. Oral mechanical bowel preparation is mandatory and patients with signs of peritonitis are excluded. The C-seal student team will perform the randomization procedure, supports the operating surgeon during the C-seal application and achieves the monitoring of the trial. Patients are followed for one year after randomization en will be analyzed on an intention to treat basis.

**Discussion:**

This Randomized Clinical trial is designed to evaluate the effectiveness of the C-seal in preventing clinical anastomotic leakage.

**Trial registration:**

NTR3080

## Background

Anastomotic Leakage (AL) is the most important complication after colorectal surgery and leads to high rates of morbidity, prolonged hospitalization, commonly requires re-interventions, and can result in death [1].

The incidence of AL varies in the literature between 4 and 20% [2-6]. This considerable variation may be due to the fact that different definitions are used. The International Study Group of Rectal Cancer (ISGRC) proposed a standardized definition for AL according to clinical grading [7]. AL is defined as a defect of the intestinal wall at the anastomotic site leading to a communication between the intra and extraluminal compartments. An abscess in the proximity of the anastomosis is considered to be AL. The severity of AL is classified in three grades. Grade A AL corresponds to the definition ‘radiologic leakage’ for which no intervention is required. Grade B AL requires an active therapeutic intervention but could be managed without relaparotomy. Grade C AL requires a relaparotomy [7].

Recent data from the Dutch Surgical Colorectal Audit (DSCA) showed an AL rate of 11% leading to re-intervention in the Netherlands [8].

In order to reduce the incidence of AL the C-seal is developed. The C-seal is an intraluminal biodegradable drain which is stapled to the anastomosis with a circular stapler [9]. The C-seal covers the intraluminal side of the anastomosis and prevents extravasation of intracolonic content to the peritoneal cavity in case of anastomotic dehiscence.

In previous studies performed in the University Medical Center Groningen (UMCG) and in some other clinics a total amount of 52 patients were treated with the C-seal. The pilot study of fifteen patients, who underwent a colorectal resection with a C-seal, showed that the application of the C-seal was feasible and there were no clinical or radiological signs of leakage [10]. Also the subsequent phase II study with 37 patients confirmed the feasibility of the C-seal by both surgeons and by patients. There were no serious adverse events reported related to the C-seal [11]. Furthermore this study showed promising results in the reduction of clinical AL, which led to the initiation of a randomized controlled trial, the C-seal trial. This trial aims to compare the outcome for stapled colorectal anastomoses made with and without a C-seal.

The main objective of the C-seal trial is to evaluate the efficacy of the C-seal in reducing AL in stapled colorectal anastomoses, as assessed by AL leading to invasive intervention within 30 days postoperative.

## Methods

### Design

The C-seal trial is a prospective multi-center randomized controlled trial, initiated by the department of surgery, division of abdominal surgery of the UMCG, the Netherlands. The study will be performed in approximately 35 clinics.

In this trial 616 patients will be randomized equally between the C-seal group and the control group. The study protocol is approved by the central medical ethics committee of the UMCG. In all participating centers a local feasibility agreement is arranged. Patients will be followed until one year after randomization.

### Participants

Eligible patients are diagnosed with any colorectal disease requiring a colorectal anastomosis in an elective setting, have a minimum age of 18 years and an ASA classification < 4. Preoperative mechanical bowel preparation is mandatory, but can be omitted if the patient has a previously created deviating ostomy that will remain in situ. Patients with clinical signs of peritonitis and patients who underwent major surgery 30 days prior to the operation or have major surgery planned within 30 days after the procedure, are excluded.

All eligible patients visiting the surgical outpatient department in participating centers will be informed about the trial. Informed Consent must be obtained before inclusion.

The participating study sites should comply with the recent guidelines of the Dutch Society of Surgery to perform colorectal surgery (Normering Chirurgische behandeling. NVvH January 2011). The operating surgeons are adequately trained in the application of the C-seal.

### Intervention

Fifty percent of the study population will be randomized to the C-seal group and 50% to the control group. The C-seal is stapled to the anastomosis with a circular stapler. Before creating the anastomosis the C-seal is attached to the anvil of the circular stapler (Figure 1) and together they are inserted in the proximal bowel loop. After firing the circular stapler the C-seal is stapled to the mucosal side of the afferent loop (Figure 2). When the stapler is removed from the anus, the C-seal is brought through the anus and cut from the stapler anvil. The application of the C-seal to the anvil is trained in a practicum session provided to the participating operating surgeons and local research group.

**Figure 1 F1:**
[figure not shown]
C-seal attached to the anvil of the circular stapler.

**Figure 2 F2:**
[figure not shown]
Intraluminal attachment of the C-seal after the staple procedure.

Postoperatively the C-seal will be in situ for approximately two weeks. The C-seal degrades in time and secretes through the anus together with bowel contents.

### Outcome

The primary endpoint of the C-seal trial is the incidence of AL leading to invasive treatment within 30 days after surgery. AL is defined based on the classification according the ISGRC classification.

Secondary endpoints are the number of dismantled anastomoses, the number of ostomies created, the number of ostomies present after 1 year, the total duration of hospital stay, the interval between primary surgery and the diagnosis of AL, the incidence of late AL (≥ 30 days and within 1 year) and a differentiation between grade A, B or C AL classified according the ISGRC [7].

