### Randomization

Patients are equally distributed to either the C-seal or the control group. In an attempt to overcome possible bias, the randomization procedure is performed in the operating room during surgery. The randomization procedure is performed by a C-seal student with an online randomization system. The randomization is stratified for center, high or low anastomosis (respectively proximal or distal of the peritoneal reflection) and the intention to create a temporary deviating ostomy.

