### Statistical analysis

Primary and secondary endpoints will be analyzed on an intention to treat basis. The groups will be compared by means of a Fisher’s exact test.

After 50% and 75% of patient enrollment an interim analysis will be performed based on Snapinn’s stopping rule [12].

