## Discussion

This study investigates the efficacy of the C-seal in the prevention of clinical AL in stapled colorectal anastomoses. The concept of the protection of a colorectal anastomosis by means of an intraluminal device has already been described [13-15]. Based on the idea that intraluminal devices in colorectal anastomoses protect the fecal stream from anastomotic contact, there will be no leakage if anastomotic dehiscence develops. Under the device a perforation can still arise, but because there is no fecal spill this probably will not lead to a fecal peritonitis. Local inflammation may cause adhesions and cover the defect and symptoms of a possible leak are probably less severe [13,16].

It is also hypothesized that AL in colorectal anastomoses is frequently caused by poor vascularization through intraoperative mechanical manipulation [17,18], often from the distal rectal stump [19]. Since the C-seal is attached to the proximal bowel loop, the C-seal remains in situ if the rectal stump is poorly vascularized and leads the fecal stream in the first postoperative weeks outside the body without contact with the rectal wall. After about two weeks the biodegradable drain degrades and is excreted through the anus.

In this study the required sample size is determined based on the current AL rate in the Netherlands. To give a good reflection of the colorectal surgery in the Netherlands and in order to approach this AL incidence, 35 different hospitals, ranging from small referral hospitals to academic centers, are participating in the trial. The participation of this large number of clinics creates possible challenges in protocol adherence. To standardize procedures all operating surgeons are trained by the C-seal research team from the UMCG and during the surgery a student from the C-seal team attends the procedure. To overcome a possible bias regarding the participation of many clinics the randomization is stratified for center.

In addition to the stratification for center, there is also stratified for the intention to create a deviating ostomy and for anastomotic height. The stratification for the intention to create a deviating ostomy is performed to prevent selection bias. The outcome of randomization (C-seal or not) may influence operating surgeons in their decision to create a deviating ostomy. Therefore, the intention to create a deviating ostomy must be documented before the patient is randomized at the OR.

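### Both ostomy endpoints are compared as plain totals, without using the ostomy intention recorded before randomisation, so a device effect may be diluted

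*Protocol article*

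**What the plan says.** Under Outcome, the protocol article lists "the number of ostomies created, the number of ostomies present after 1 year" as secondary endpoints. It does not separate ostomies by reason or by timing relative to randomisation.

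Under Statistical analysis, "Primary and secondary endpoints will be analyzed on an intention to treat basis", and "The groups will be compared by means of a Fisher" exact test. No stratified or adjusted analysis is mentioned.

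Three other places bear on what the totals contain:

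- Randomization: one stratification factor is "the intention to create a temporary deviating ostomy".
- Discussion: "the intention to create a deviating ostomy must be documented before the patient is randomized at the OR". The reason given is that "The outcome of randomization (C-seal or not) may influence operating surgeons in their decision to create a deviating ostomy".
- Participants: bowel preparation "can be omitted if the patient has a previously created deviating ostomy that will remain in situ", so some patients may enter with an ostomy that stays.

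**The concern.** A patient whose surgeon already intends an ostomy will usually get one in either arm. Such patients add equally to both arms' totals and carry little information about whether the device spares patients an ostomy after leakage. A test on the total that ignores intention treats this predictable component as noise. At 1 year the same applies to intended ostomies not yet reversed and to ostomies that were present at entry and remain.

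The trial already collects the variable that would separate these components and balances the arms on it. At stake is whether a real reduction in leak-related ostomies would be visible, and whether a difference in the total could be explained. A lower total in the C-seal arm could come from fewer leaks or from surgeons omitting intended ostomies once C-seal is allocated. The total alone cannot tell these apart.

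**Working it through.** **The plan's own figure.** The article gives no power for the ostomy endpoints, only 616 patients for leakage of 10% versus 4%, 90% power and 5% significance. The usual formula is n per arm = [z_α√(2p̄(1−p̄)) + z_β√(p₁(1−p₁)+p₂(1−p₂))]²/(p₁−p₂)², with p̄ = 0.07. One-sided, this is (1.645×0.3608 + 1.282×0.3583)²/0.0036 ≈ 308 per arm, or 616. Two-sided it gives 378 per arm, or 756. So 616 matches a one-sided test; that is a separate matter. At 308 per arm, two-sided Fisher power for 10% versus 4% is 80%. This is the reference when no ostomy is planned and every leak leads to one.

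**Inputs.** From Design: "616 patients will be randomized equally between the C-seal group and the control group", so 308 per arm. From Sample size: leakage of 10% and 4%. Assumed, because the article gives no values: q, the share with a planned ostomy (the same in both arms, all made), and r, the share of leaks leading to an ostomy. Each endpoint is taken as yes/no per patient.

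**Ostomies created.** Total rate = q + (1−q)×leak rate×r. For q = 0.40 and r = 1:

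- control: 0.40 + 0.60×0.10 = 46.0%
- C-seal: 0.40 + 0.60×0.04 = 42.4%
- relative risk: 0.424/0.460 = 0.92, against 0.04/0.10 = 0.40 among patients without intention.

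The alternative uses only patients without intention, 308×(1−q) per arm: 246, 185 and 123. Exact power of the two-sided 5% Fisher test:

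| r | q | Total rates | Power, total | Power, patients without intention |
|---|---|---|---|---|
| 1 | 20% | 28.0% v 23.2% | 24.7% | 70.4% |
| 1 | 40% | 46.0% v 42.4% | 12.5% | 55.2% |
| 1 | 60% | 64.0% v 61.6% | 8.1% | 35.2% |
| 0.5 | 20% | 24.0% v 21.6% | 9.3% | 35.4% |
| 0.5 | 40% | 43.0% v 41.2% | 6.2% | 24.2% |
| 0.5 | 60% | 62.0% v 60.8% | 5.2% | 13.5% |

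Counting unintended ostomies over all 308 per arm gives nearly the same: 69%, 55% and 36% for r = 1.

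**Keeping the total but stratifying.** Take q = 40%, r = 1 and 95% of intended ostomies made in both arms. A Mantel-Haenszel test of the total, stratified by intention (185 and 123 per arm, simulated), has about 46% power without continuity correction and 39% with it. Both are well above 12.5%. The gain shrinks if intended ostomies are made less consistently: with 90% made, the uncorrected figure is about 37%.

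**Ostomies present at 1 year.** Let f be the share of planned ostomies still present and g the share of leak ostomies that persist, with every leak leading to an ostomy. Rate = leak×g + (1−leak×g)×q×f. For q = 40%, f = 10%, g = 1: 0.10 + 0.90×0.04 = 13.6% versus 0.04 + 0.96×0.04 = 7.8%. Fisher power at 308 per arm, q = 40%:

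| f | g = 1 | g = 0.5 |
|---|---|---|
| 0% | 80% | 46% |
| 10% | 59% | 23% |
| 20% | 45% | 16% |
| 30% | 36% | 13% |

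Pre-existing ostomies that remain act like a higher q×f.

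**Changed decisions.** As an illustration, suppose 40% are intended and one in five of these is omitted in the C-seal arm only. The total there falls by 0.40×0.20 = 8 points. The leak-driven difference at the same q with r = 1 is 46.0 − 42.4 = 3.6 points.

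**The case against.** The strongest reply has four parts.

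- **The total is a legitimate endpoint.** It matters to patients, and under intention to treat it captures any effect of allocation on the surgeon's decision, which the Discussion expects may occur. This stands, and is why the total should stay. An endpoint limited to unintended ostomies would miss intended ones that were omitted.
- **Stratified randomisation already balances intention.** This stands as far as it goes: planned ostomies should be similar in the two arms, so the main problem is lost power, not bias. Balance at randomisation does not recover the power if the analysis ignores the stratum.
- **These are secondary endpoints without a power claim, and a condensed article may leave detail to a fuller document.** This limits the weight of the point. The article does, however, state the endpoints and the test, and as stated they do not use the intention.
- **The figures are assumed.** This stands. Setting r = 1 is probably the upper end, since the Background says grade B leaks can be managed without relaparotomy. At r = 0.5 the narrower endpoint is itself weak.

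A reader might infer more than the article supports. Pre-existing ostomies do not count as created in the trial; they can affect only the 1-year count. The article gives no rule that deaths before 1 year count as free of an ostomy, and does not say how an ostomy in situ is coded for stratification. Nor can intended ostomies be called beyond the influence of allocation, since the Discussion says the opposite may happen.

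**Conclusion.** The point holds as avoidable dilution in two secondary endpoints. As stated, the analysis of totals ignores a variable that is recorded before randomisation and used to stratify it. For ostomies created, with 20% to 60% planned, power for the total is about 25% down to 8% if every leak leads to an ostomy, and about 9% down to 5% if half do. Among patients without intention it is about 70% down to 35%, and about 35% down to 13%, respectively.

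At 1 year the loss may be small if most intended ostomies are reversed, and is substantial if many remain. It would go too far to say that a real effect is bound to be swamped: the planned share, the leak-to-ostomy share and the reversal rate are all assumptions. Nothing here touches the primary endpoint.

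**What to change.** - Analyse both ostomy endpoints stratified by documented ostomy intention, for example with a Mantel-Haenszel or exact stratified test.
- Prespecify, as a separate endpoint, ostomies that were neither intended nor in situ at randomisation.
- Report departures from intention by arm in both directions: unintended ostomies made and intended ostomies omitted.
- Keep the total counts, because allocation may itself change the surgeon's decision.

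Intention is already recorded, so the cost is some endpoint wording and a little more analysis. The change should be fixed before outcome data are seen by arm, since a split chosen afterwards would be post hoc.

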### Sample size

The sample size of 616 patients is determined with a power analysis based on a power of 90%, a significance level of 5%, AL percentage of 4% in the C-seal group and 10% AL in the control group.

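### Two secondary endpoints are durations, but the only named test is Fisher's exact test, and the interval to leak diagnosis exists only for patients who leak

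*Protocol article*

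**What the plan says.** The Outcome section of the protocol article has a binary primary endpoint, AL leading to invasive treatment within 30 days. Most secondary endpoints are counts or categories: dismantled anastomoses, ostomies created, ostomies present at one year, late AL and AL grade. Two are durations: "the total duration of hospital stay" and "the interval between primary surgery and the diagnosis of AL".

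The Statistical analysis section then states "Primary and secondary endpoints will be analyzed on an intention to treat basis", followed directly by "The groups will be compared by means of a Fisher’s exact test". No other between-group test is named, and neither sentence exempts an endpoint or is limited to the binary ones. The article does not say how a patient without AL enters the interval endpoint.

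**The concern.** Two things do not fit together.

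- **The test.** Fisher's exact test works on counts in a contingency table. Hospital stay and an interval in days would first have to be dichotomised. No cut-off is stated, and one chosen after the data are seen would be a data-dependent choice.
- **The population.** Hospital stay exists for every operated patient, so only the test is at issue there. The interval to diagnosis exists only if a leak occurs. Leaking happens after randomisation and is the very event the device is meant to prevent. Randomisation therefore no longer protects a comparison between leakers of the two arms.

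The second point matters for this device because the article says the drain stays in place for about two weeks and then degrades. If protection is limited to that period, early leaks are removed from the C-seal arm and later ones are not. The remaining C-seal leaks then look later, although no patient's leak was delayed. A reader could take this as evidence of postponement.

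**Working it through.** **Inputs from the protocol article**
- Size and allocation (Design): "In this trial 616 patients will be randomized equally between the C-seal group and the control group", so 308 per arm.
- Error rates (Sample size): "a power of 90%, a significance level of 5" percent; the article does not state whether this is one-sided or two-sided.
- Leak rates (Sample size): "AL percentage of 4% in the C-seal group and 10% AL in the control group".
- Literature range (Background): "The incidence of AL varies in the literature between 4 and 20" percent.

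**Step 1. Reproduce the plan's figure.** With p1 = 0.10, p2 = 0.04 and mean 0.07, the pooled-variance formula without continuity correction is

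n per arm = [z_α √(2 × 0.07 × 0.93) + z_β √(0.10 × 0.90 + 0.04 × 0.96)]² / 0.06².

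With a one-sided 5% level (1.645) and 90% power (1.282): (1.645 × 0.3608 + 1.282 × 0.3583)² / 0.0036 ≈ 308 per arm, 616 in total. This matches. The two-sided version gives 756. Sidedness is a separate matter and nothing below depends on it.

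**Step 2. How many patients have an interval?**
- Control: 308 × 0.10 = 30.8.
- C-seal: 308 × 0.04 = 12.3.
- Together: 43.1 of 616 = 7%, so about 93% have no value.

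These rates concern AL leading to re-intervention within 30 days; grade A and late leaks would add some patients. As an assumed range, let the control rate run from 4% to 20% and keep the 10:4 ratio:
- Lowest: 308 × (0.04 + 0.016) = 17.2, or 2.8% of 616.
- Highest: 308 × (0.20 + 0.08) = 86.2, or 14% of 616.

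So about 86% to 97% of randomised patients have no value.

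**Step 3. What could 31 versus 12 show?** The standardised difference detectable with 80% power at two-sided 5% (normal approximation) is (1.960 + 0.842) × √(1/31 + 1/12) = 2.802 × 0.340 = 0.95 SD. Only a large difference would be seen.

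**Step 4. Can the leaker-only comparison be biased?** The article gives no leak-time distribution, so everything in this step is assumed. Leak times follow a gamma distribution, 10% of control patients leak, and C-seal removes a share of leaks up to day 14 while leaving all other leak times unchanged. No leak is delayed in any scenario. The leakers are compared by a two-sided 5% rank (Mann-Whitney) test, which the article does not name.

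| Assumed leak times | Share of early leaks removed | Median, control vs C-seal leakers (days) | Rejections |
|---|---|---|---|
| shape 4, mean 7 days | 65% | about 6.5 vs 6.9 | 6% to 7% |
| shape 2, mean 7 days | 65% | about 6.0 vs 7.2 | 10% |
| shape 2, mean 7 days | 70% | about 5.9 vs 7.7 | 13% |
| shape 2, mean 9 days | 70% | about 7.6 vs 11.3 | 23% to 25% |
| shape 2, mean 12 days | 70% | about 10.2 vs 15.6 | 35% to 36% |
| shape 2, mean 9 days, removal unrelated to timing | 60% of all leaks | about 7.6 vs 7.7 | 4% to 5% |

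Ranges in the last column are the spread between repeated runs. The bias comes from time-limited protection and vanishes when prevention is unrelated to timing. Its direction follows from the selection; its size depends on the assumed leak times.

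**The case against.** **The article condenses a fuller plan.** Tests for single secondary endpoints, and the handling of patients without a leak or of in-hospital deaths, are details an article may leave to the full protocol or analysis plan. This stands as far as omissions go, so the lack of a death rule for hospital stay is not counted here. What remains is a positive statement: one basis and one test, with no exception, that cannot be applied to two listed endpoints.

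**Fisher's test was probably meant for the categorical endpoints.** That is quite possible, since the primary and most secondary endpoints are categorical. If so, one limiting clause settles that half of the point. It does not settle the analysis population for the interval.

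**A reader might infer that the interval can never be analysed by intention to treat.** The documents do not support that. The article does not say that the interval is to be compared among leakers only; this follows from its definition. Recast as time to AL in all randomised patients, it can be analysed by intention to treat.

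**A reader might also infer that the trial cannot tell prevention from postponement.** That goes too far. The Outcome section lists late AL, from 30 days to one year, which is a binary endpoint in all randomised patients to which Fisher's test applies. Together with the 30-day primary endpoint it covers postponement beyond day 30. Only timing within the first 30 days is uncovered.

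**The simulated bias rests on invented leak times.** This stands. No single rejection rate should be quoted as the size of the problem; at the low end of the range it is close to the nominal 5%.

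**Conclusion.** The point holds as a limited one. As written, Fisher's exact test does not fit hospital stay or the interval to diagnosis without a cut-off. As defined, the interval exists for about 43 of 616 patients (31 versus 12; 7%, or about 3% to 14% over the assumed range of control rates). A between-arm comparison of it is not an intention-to-treat comparison. It can mislead if protection lasts only as long as the drain, with about 6% to 36% rejections under the assumed leak times although nothing is delayed.

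The counts rest on the protocol's own design rates; the bias figures rest on assumptions that the article neither supports nor contradicts. The primary endpoint is binary and suits Fisher's test, and the sample size is not touched by this point. This is a cheap improvement to two secondary endpoints, not a threat to the trial's main conclusion.

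**What to change.** - Limit Fisher's exact test to the categorical endpoints.
- Analyse AL timing as cumulative incidence from surgery to one year in all randomised patients, with death without AL as a competing event, for example by Gray's test. Report the estimates at 30 days and at one year.
- Report the interval among leakers descriptively, without a test.
- Compare hospital stay with a rank-based test, for example one stratified by the randomisation factors (van Elteren). A rule for in-hospital death in that analysis is optional detail.

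Other methods of the same kind would serve equally well. The cost is a change of analysis wording and slightly more analysis work. The listed interval already requires the leak date, and one-year follow-up is already planned.
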